#### First phase

2.6.1

In the first phase of our intervention the quality of life of participants, their respiratory health status, and their level of anxiety will be measured using specific tools. Participants’ skills and expertise will be evaluated by an educational diagnosis. The hospital register of each participant will be consulted to collect the number of hospitalizations and emergency room visits during the year preceding the intervention. Patients will be asked, at the end of the session, to complete sheet 1 of the evaluation that includes 4 parts about their perception of the acceptability, adequacy, adoption, and cost of the program.

A 2-part sheet about the cost and fidelity will be completed by 2 researchers. The cost part will be completed by the principal investigator after each nursing consultation. The fidelity part will be completed by a second researcher who will be invited to participate in the evaluation of the program. All sessions will be video or audio recorded to facilitate this task (Fig. 3).

#### Second phase

2.6.2

At this phase 6 educational sessions will be conducted at the patients’ place. Before each session, patients will be required to complete a 5-question questionnaire, to assess their knowledge of the topic. At the end of each session, patients will have to fill the same questionnaire again to evaluate their short-term learning. They will also be required to evaluate the acceptability and cost of the session. An open-ended question is added to explore the participant's perception of the education session. After each session, researchers will complete their evaluation sheet.

#### Third phase

2.6.3

During this last session that takes place at the nurse's office, quality of life of participants, their respiratory health status, and their level of anxiety will be reevaluated. A second educational diagnosis will be performed and compared to the first one. At the end of the session, patients will be asked to complete sheet 2 of the evaluation that includes 4 parts about their perception of the acceptability, adequacy, adoption, and cost of the program.

#### Phone call follow up

2.6.4

One month after the last intervention, using the phone, a third evaluation of the quality of life of participants, their respiratory health status, and their level of anxiety will be performed by the principal investigator who will also identify the rate of re-hospitalization and emergency visits for each participant in the month that follows the end of the intervention. The principal researcher will then complete the cost part of the 2-part sheet.

Researchers will complete the first part concerning the cost, which will be completed by the principal investigator. A second researcher will complete the fidelity part in addition to the Loln questionnaire that assesses coverage.

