**Figure 2 F2:**
[figure not shown]
Progress of the intervention.

**Phase I:** At the end of a medical consultation, the doctor will offer the patient the opportunity to benefit from a nursing consultation and remote monitoring to better manage his COPD. A nursing consultation will be scheduled during which the nurse will explain the procedure, obtain the written consent of the patient, and develop an educational diagnosis with the participation of the patient. This step consists of a motivational interview that constitutes a guided, person-centered approach aiming at making patients aware of their behavior and consider actions to change it if it adversely affects their health. The nurse will explain how the patient should use the oximeter to measure daily the oxygen saturation (SaO2) and pulse, and how the information collected will be transmitted. An appointment will then be made for a first meeting at the patient's home.

**Phase II:** During the next 6 weeks the patient will receive one visit per week from the nurse to encourage him/her to self-assess each of his/her risk factors so that he/she becomes aware that his/her illness is not inevitable and that he/she can be involved in a behavioral change to reduce the risk of exacerbations. During these 6 weeks, a telephone number will be available to the patient in case of emergency and for any additional information.

**Phase III:** Following the 6 educational sessions delivered by the nurse, a final consultation will be scheduled at the nurse office to evaluate the patient's achievements and modify his/her educational assessment. A telephone follow-up will be conducted after one month to assess the maintenance of learning.

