### Outcome measures

2.5

Based on Proctor's lists of outcome variables that can assess program implementation,^[26]^ this study will evaluate the acceptability, adoption, adequacy, fidelity, cost, and coverage of the intervention, using various tools: the “Pre-Referral intervention team inventory” will be adapted to study the acceptability of the intervention,^[27]^ the “adoption of information technology innovation” scale for adoption,^[28]^ the “Parenting strategies questionnaire” for adequacy,^[29]^ the “Utilization and Cost Questionnaire” for cost,^[30]^ and the “levels of institutionalization” scale for coverage.^[31]^ With regard to fidelity, no evidence-based instrument could be identified; thus, the fidelity will be assessed by comparing the protocol of the intervention with what will be done in the field, the education sessions will be videotaped and a second researcher will be invited to evaluate the fidelity.

To evaluate the impact of the intervention, many pre-tests will be performed before starting it: the COPD assessment test (CAT)^[32]^ to evaluate the quality of life of participants, the COPD clinical questionnaire (CCQ)^[33]^ to evaluate their respiratory health status, and the “Hospital Anxiety and Depression” (HAD) scale to measure the anxiety.^[34]^ Skills and expertise of the participants will be assessed using questions created for each session and comparing the pre- and post-intervention educational diagnosis. The hospital register of each participant will be consulted to collect and evaluate the number of hospitalizations and emergency room visits during the year preceding the intervention and during the intervention.

All these measurements will be grouped into evaluation sheets. There will be sheets to collect data from participants, and others to collect data from researchers so that the program can then be evaluated.

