#### Social desirability bias (Hawthorne effect)

2.9.3

It is defined by the observed positive effect that is not related to the intervention but simply due to the fact that this group feels observed, hence the modification of its behavior. This limitation can be observed in our study since the protocol design does not include a blind group. A telephone follow-up is therefore considered 1 month after the intervention to evaluate the maintenance of the acquired skills.

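### At one month the CAT, CCQ and HAD move from visit to telephone for every patient, so a mode shift cannot be separated from kept or lost benefit

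*Protocol article*

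**What the plan says.** Section 2.5 names the three instruments: the CAT for quality of life, the CCQ for respiratory health status and the HAD for anxiety. They are used three times.

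- **First.** In section 2.6.1 (First phase) the three domains, ending with "their level of anxiety will be measured using specific tools", are assessed in Phase I. Section 2.4 describes the contact in that phase: "A nursing consultation will be scheduled during which the nurse will explain the procedure, obtain the written consent of the patient". Taking written consent implies that it is face to face.
- **Second.** Section 2.6.3 (Third phase): "During this last session that takes place at the nurse's office, quality of life of participants, their respiratory health status, and their level of anxiety" are assessed again.
- **Third.** Section 2.6.4 (Phone call follow up): "One month after the last intervention, using the phone, a third evaluation of the quality of life of participants" is carried out, along with the other two domains. The same sentence names the assessor: "their level of anxiety will be performed by the principal investigator who will also identify the rate of re-hospitalization and emergency visits".

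Section 2.1 describes a single intervention group with two researchers collecting data, and section 2.7 sets the sample at 30. Section 2.4 gives the call the purpose of checking that learning has lasted. Section 2.9.3 returns to the call under social desirability: "A telephone follow-up is therefore considered 1 month after the intervention", there to see whether acquired skills are kept. The limitations in section 2.9 do not mention the move from visit to telephone.

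**The concern.** A questionnaire answered over the telephone need not give the same score as one completed at a visit, even when the patient's state has not changed. Here the mode changes once, for everyone, at the one time point meant to show what happens after the weekly home visits have ended. If scores worsen at one month, the cause could be loss of benefit or the telephone. If they hold steady, the benefit may have lasted, or a telephone shift may have covered a decline.

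The third aim of the study is to make recommendations for a randomised trial. A misleading picture of durability could carry into the choice of endpoint, follow-up time or expected effect for that trial.

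**Working it through.** **Inputs from the protocol article:** one group (2.1); 30 patients (2.7); three assessments, with modes visit, visit, telephone (2.4, 2.6.1, 2.6.3, 2.6.4). No alpha, power, SD or expected change is given for the CAT, CCQ or HAD, and 30 comes from a pilot-study range of 10 to 40. There is therefore no figure of the plan's own to reproduce beyond noting that 30 lies in that range.

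**Step 1: can mode be separated from time?** Write the expected scores as

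- first: μ
- second: μ + β₂
- third: μ + β₃ + δ

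Here β₂ and β₃ are true changes from baseline and δ is the effect of telephone instead of visit. The design rows for (μ, β₂, β₃, δ) are (1,0,0,0), (1,1,0,0) and (1,0,1,1). The last two columns are identical, so the matrix has rank 3 for 4 parameters. The contrasts are:

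- second minus first = β₂, free of δ
- third minus second = (β₃ − β₂) + δ
- third minus first = β₃ + δ

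Both contrasts that use the one-month score carry δ in full. With no control group and no telephone score at another time point, nothing in the data estimates δ.

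**Step 2: how much could it matter?** The documents give no mode effect, so the shifts below are assumptions, in units of the SD of within-patient change. I assume all 30 patients are assessed and a two-sided 5% paired t-test, with 29 degrees of freedom, critical value 2.045 and noncentrality d × √30. The 95% confidence interval half-width is 2.045/√30 = 0.37 SD.

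No true change, telephone shift only, in either direction:

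| Assumed shift (SD) | Probability of a significant change |
|---|---|
| 0 | 5% (nominal) |
| 0.1 | 8.3% |
| 0.2 | 18.5% |
| 0.3 | 35.5% |
| 0.5 | 75.4% |

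True loss of 0.5 SD, telephone answers more favourable:

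| Assumed offset (SD) | Net observed loss (SD) | Probability of detecting it |
|---|---|---|
| 0 | 0.5 | 75.4% |
| 0.2 | 0.5 − 0.2 = 0.3 | 35.5% |
| 0.3 | 0.5 − 0.3 = 0.2 | 18.5% |

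A shift of 0.2 to 0.3 SD is smaller than the half-width of 0.37 SD, so it would not stand out in the results, yet it could create or hide a change.

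**Step 3: is a change of interviewer also shown?** For the second assessment, section 2.6.3 says only "quality of life of participants, their respiratory health status, and their level of anxiety will be reevaluated", and section 2.6.1 is equally silent on who administers the forms and whether patients complete them alone. Section 2.6.1 does have the principal investigator filling in a cost sheet after each nursing consultation, so the same person may collect the scores at all three times. The change of mode is established. The change of interviewer is not.

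**The case against.** **This is a feasibility study.** Section 2.8 bases feasibility on six implementation variables, none of which is the CAT, CCQ or HAD. The abstract describes the measures as pre and post, and that contrast does not involve the call. This stands, and it limits the point to the one-month reading.

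**Without a control group, the one-month change could not isolate durability anyway.** Also true: the mode change is one threat among several. But it is introduced by a stated choice, and it is cheap to remove.

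**An article leaves assessor and form of administration to the full protocol, and Figures 2 and 3 are not shown.** This is fair, so their absence is not the finding. The move from office to telephone is stated in the text and does not depend on those details.

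**Readings that go too far.** A reader might infer that the interviewer changes at one month; the documents do not say who made the first two assessments. A reader might infer that patients will answer the principal investigator more favourably, so that decline is hidden. If the earlier forms were also completed by interview, social desirability could be as strong or stronger at the final visit, and the shift could run the other way. A reader might also infer that section 2.9.3 contradicts itself by offering the call as a cure for socially desirable answers. It ties the call to retention of skills, not to the CAT, CCQ or HAD scores.

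**Conclusion.** The point holds for mode. In this single-group design the switch from visit to telephone coincides completely with the one-month time point, so it cannot be separated from maintenance or loss of benefit in the CAT, CCQ and HAD. The confounding follows from the stated design and needs no numerical assumption beyond reading the Phase I consultation as face to face.

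Its size and direction are unknown, and no figure in CAT points can be taken from the documents. Under the assumptions shown, a shift of 0.2 to 0.3 SD of change would raise false signals from 5% to between 18.5% and 35.5%, or cut detection of a true 0.5 SD loss from 75.4% to between 35.5% and 18.5%.

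The baseline to final-visit comparison is not affected. This is a worthwhile, low-cost improvement to the follow-up and does not undermine the study's feasibility aims.

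**What to change.** In sections 2.6.1, 2.6.3 and 2.6.4, specify one patient self-completed format for the CAT, CCQ and HAD at all three times.

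- **Third assessment.** Give each patient a dated set of forms at the final consultation, to be filled in at home on the day of the call, before it starts. The forms are then returned, or only the marked answers are read out. Return is the cleaner option, since reading out still discloses the answers to study staff.
- **Assessor.** Have the same researcher collect the scores at all three times, preferably one who does not deliver the sessions. Changing the assessor for the third assessment alone could create the very confounding to be avoided. If the second researcher is chosen, note that this person also judges fidelity (2.6.1, 2.9.4).
- **Exceptions.** Flag any one-month score that had to be obtained by interview, and report the one-month change with and without those scores.

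If the format cannot be changed, list the move from visit to telephone as a limitation in section 2.9.

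**Cost:** printing 30 sets of forms, and a few patients may not have the form ready. No extra visit is needed. The difference between office and home remains, as does the lack of a control group.

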### Sample size calculation

2.7

Since this is a feasibility study with an intervention that has never been tested before on the Lebanese population, no formal calculation of the sample size will be performed, and 30 patients with moderate to severe COPD will be recruited, based on Hertzog's recommendations: a sample of 10 to 40 people is sufficient for a pilot study using a single group to estimate sample size for a future trial.^[35]^

### Analyses

2.8

To determine the feasibility of this research program, 6 variables will be selected: acceptability, adoption, adequacy, fidelity, cost and coverage, with 2 types of participants: COPD patients and researchers. Patients will assess acceptability, adoption, adequacy and cost, while researchers will assess the fidelity, cost and coverage of the program.

Analyses will be performed on SPSS version 25 (IBM SPSS Statistics for Windows). Student *t* test will be used to compare normally distributed continuous variables between 2 groups, ANOVA test between 3 groups or more, and Chi-square for binary and/or categorical variables. Open ended questions will be analyzed narratively.

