### Design

2.1

This study aims to evaluate the feasibility, acceptability and pre-test the impact of a nursing consultation and tele-monitoring in Lebanon. It will be conducted at the Hôtel-Dieu de France (HDF) hospital, one of the largest university hospitals in Beirut, and will use quantitative and qualitative methods in pre- and post-intervention to collect data over a period of 3 months with a single group intervention. Data will be collected by 2 researchers. A consent form will be signed by each participant before the intervention. Patients will be informed about the purpose of the study, the course of the intervention, and the freedom to withdraw from the study at any time. Their consent for the video recording will also be taken.

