## Discussion

3

As the prevalence of COPD continues to increase, so does its cost to the healthcare system. Self-management has been shown to be an effective component of chronic care, yet the impact of tele-monitoring has not been yet established as a support for a self-management program. This proposed intervention may improve the quality of life and reduce emergency visits and re-hospitalization rates of Lebanese patients with COPD; it may also be extended to COPD patients in any developing country with no specific educational program for this population.

Results of this innovative study in Lebanon will establish feasibility and provide preliminary evidence on the efficacy of this intervention, and could potentially influence clinical practice and health policy in Lebanon.

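### Section 2.8 sets out to determine feasibility but names only between-group tests as quantitative methods; these do not give the level or precision of the feasibility variables

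*Protocol article*

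**What the plan says.** The article's first aim concerns feasibility and acceptability, its second is to pre-test impact, and its third is to make recommendations for a randomised study (Introduction). The Design section (2.1) describes data collection "over a period of 3 months with a single group intervention".

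The Analyses section (2.8) has two paragraphs.

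- The first states the purpose and the number of variables: "To determine the feasibility of this research program, 6 variables will be selected". It then names them and assigns raters. Patients rate acceptability, adoption, adequacy and cost; researchers rate fidelity, cost and coverage.
- The second names the software and the methods. Student's t test is to "compare normally distributed continuous variables between 2 groups, ANOVA test between 3 groups or more, and Chi-square for binary and/or categorical variables". It ends: "Open ended questions will be analyzed narratively".

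Section 2.9.2 adds that all included patients will be analysed, whether or not they complete. No section names a proportion, mean, median or interval for any of the six variables.

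The sample size section (2.7) makes no formal calculation. It supports 30 patients by a rule that 10 to 40 are enough in a single-group pilot for estimating the size of a later trial. The Discussion (section 3) states: "Results of this innovative study in Lebanon will establish feasibility".

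**The concern.** Feasibility is a question of level: what share of patients find the programme acceptable, how fully the sessions follow the protocol, what it costs. A comparison test answers a different question, namely whether two or more sets of values differ. With one group there are no arms to compare. Where a variable is rated twice, the test addresses change between ratings, and a programme can be stably poor or stably good.

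The stake is the hand-over to the randomised study. If the quantitative output is a set of test results, the recommendations will rest either on p-values that do not bear on feasibility or on bare values from 30 patients read as if they were exact. The study's size is justified by an estimation purpose, so an analysis built on tests does not match its rationale.

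**Working it through.** **The plan's own figure.** The number 30 cannot be reproduced by formula, because the article gives no error rate, power, effect size or SD and says that no formal calculation is made. It lies inside the range of 10 to 40 that section 2.7 relies on. No stated number is wrong on this point.

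**What can be compared, variable by variable.**

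| Variable | Rated by | When (sections 2.6.1 to 2.6.4) |
|---|---|---|
| Acceptability | patients | sheet 1, each home session, sheet 2 |
| Adoption, adequacy | patients | sheets 1 and 2 |
| Cost | patients and researchers | sheets 1 and 2, each session; researchers also at follow-up |
| Fidelity | second researcher | recorded sessions, against the protocol |
| Coverage | second researcher | apparently once, at the end |

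Change tests are therefore possible for the four patient-rated variables. Fidelity is a degree of adherence, and coverage appears to be a single rating of the programme.

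**What a test does not report.** Assume acceptability is reduced to yes or no, and compare sheet 1 with sheet 2 as two sets of 30. The rates are illustrative; the article gives none.

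- 9/30 at both times: chi-square = 0, p = 1.0. Level 30%, exact 95% CI 14.7% to 49.4%.
- 27/30 at both times: chi-square = 0, p = 1.0. Level 90%, exact 95% CI 73.5% to 97.9%.

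The two test results are identical, while the two programmes could hardly differ more. A paired test would not help, since the net change is zero in both cases.

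**Precision available at n = 30.** For a proportion x/n, the exact (Clopper-Pearson) limits are:

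- lower = 2.5% quantile of Beta(x, n − x + 1)
- upper = 97.5% quantile of Beta(x + 1, n − x)

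| Assumed result | Exact 95% CI |
|---|---|
| 15/30 (50%) | 31.3% to 68.7% |
| 21/30 (70%) | 50.6% to 85.3% |
| 24/30 (80%) | 61.4% to 92.3% |
| 27/30 (90%) | 73.5% to 97.9% |
| 30/30 (100%) | 88.4% to 100% |

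Half the width is (68.7 − 31.3)/2 = 18.7 points at 50% and (92.3 − 61.4)/2 = 15.4 points at 80%.

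For a mean score or mean change, the half-width is t(0.975, n − 1)/√n SD. At n = 30 this is 2.045/5.477 = 0.373 SD.

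If 24 patients complete (20% loss, an assumption), 19/24 (79%) has an interval of 57.8% to 92.9%, and the half-width of a mean is 0.42 SD.

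**Session-level ratings.** Six home sessions for 30 patients give up to 6 × 30 = 180 ratings of fidelity and of session acceptability. Ratings of the same patient are not independent, so an interval that treats them as 180 separate observations would probably be too narrow.

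**The case against.** The strongest reply is that the two paragraphs of 2.8 are separate. The first lists the feasibility variables; the second lists tests and does not tie them to those variables. The tests may be meant for the impact aim: CAT, CCQ and HAD are measured three times (2.6.1, 2.6.3, 2.6.4), which would explain a method for three or more groups. On that reading the article is silent on how feasibility ratings are summarised, and descriptive detail is the kind of content that an article leaves to the full protocol or analysis plan.

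Much of this stands. A reader might infer that feasibility will be judged by p-values alone; the text does not say so. Nor does it support the view that the plan can say nothing about acceptance or delivery. Section 2.6.2 includes an open question on how patients saw each session, such answers are analysed narratively, and section 2.5 has a second researcher compare recorded sessions with the protocol. It would also be wrong to say that the feasibility variables have nothing to be compared with, as the table of ratings shows.

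What does not stand is that this is only missing detail. The article does choose its quantitative methods, in a section that opens with feasibility, and every one of them is a comparison. Narrative analysis gives no level for the rating scales in 2.5, and checking fidelity against the protocol is a way of measuring it, not of summarising it. The absence of a confidence interval would not be a point by itself; the mismatch between stated purpose and stated methods is.

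Two further limits are fair. Coverage, as apparently one rating by one researcher, has no meaningful interval. And the proportions used above are assumed; the adapted questionnaires may yield scores instead, in which case the half-width for a mean applies.

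**Conclusion.** The point holds for the quantitative analysis of feasibility. As written, 2.8 names no method that reports the level or the precision of acceptability, adoption, adequacy, cost or fidelity, although that is what the first aim asks and what the sample size rationale implies. At 30 patients the unreported uncertainty is material: roughly 15 to 19 percentage points either way for proportions between 50% and 80%, and 0.37 SD for a mean. These sizes rest on complete data from 30 patients and on illustrative rates. The conclusion does not depend on whether the tests are paired or on whether a threshold for success is set. It is worth correcting before analysis; nothing in the data collection needs to change.

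The Discussion's wording is stronger than such data can bear. Its sentence does call the evidence on efficacy preliminary, but that qualifier is not applied to feasibility.

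**What to change.** In section 2.8:

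- State that the main analysis of feasibility is estimation. Summarise acceptability, adoption, adequacy, cost and session-level fidelity at each rating time as a proportion, mean or median with a 95% CI, allowing for repeated sessions within a patient where they are pooled.
- Report coverage descriptively, without an interval.
- Give changes in CAT, CCQ and HAD as mean change with SD and 95% CI, since these inform the planning of the future trial.
- Say which variables the tests apply to, and treat them as secondary.

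In section 3, say that the study will estimate feasibility, so that the claim matches the precision.

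The cost is a few sentences and somewhat more reporting, with no new data or visits. The downside is that conclusions will look less certain: an assumed 80% acceptance would be published with an interval of 61% to 92%.

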**Methods::**

Validated questionnaires will be adapted to meet the context of our study in terms of acceptability, adoption, adequacy, fidelity, cost, and coverage. The impact of this program on quality of life will be measured with the COPD assessment test (CAT) and the COPD clinical questionnaire (CCQ), and the Hospital Anxiety and Depression (HAD) scale will be used to measure anxiety. All measures will be delivered pre- and post-intervention. To evaluate the impact of our program on the rate of hospitalization and emergency visits, the number of hospitalizations and emergency room visits during the year preceding the intervention will be collected from the hospital register of each participant.

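### Section 2.8 names only tests for independent groups, although the study has one group and its impact comparisons are within patient

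*Protocol article*

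**What the plan says.** Section 2.1 (Design) plans data collection "pre- and post-intervention to collect data over a period of 3 months with a single group intervention". The Methods paragraph of the abstract says of the outcome scales: "All measures will be delivered pre- and post-intervention".

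The repeated measurements on the same patients are set out in section 2.6:

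- Section 2.6.1 takes quality of life, respiratory health status and anxiety at the start.
- Section 2.6.3 takes them again at the final consultation: "quality of life of participants, their respiratory health status, and their level of anxiety will be reevaluated".
- Section 2.6.4 adds, by phone one month later, "a third evaluation of the quality of life of participants, their respiratory health status, and their level of anxiety will be performed".
- Section 2.6.2 gives a five-question knowledge form before each of six sessions. After each session, "patients will have to fill the same questionnaire again to evaluate their short-term learning".

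Section 2.8 (Analyses) is the only place where statistical tests are named. For continuous variables, the Student t "test will be used to compare normally distributed continuous variables between 2 groups, ANOVA test between 3 groups or more". For the rest it gives "Chi-square for binary and/or categorical variables". No paired, repeated-measures or other within-patient method appears anywhere in the article.

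**The concern.** The named tests compare separate sets of people and assume that observations in one set are independent of those in another. This study defines no comparison arms. The contrasts that answer its impact aim are before versus after, and across three visits, in the same 30 people. Two scores from one patient on one scale are normally positively correlated, and an independent-group test ignores that.

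What is at stake is precision. An analyst who followed section 2.8 literally would report p-values that are too large. Any interval built on the same standard error would be too wide. In a pilot of 30 that is meant to pre-test impact and inform a randomised trial, a real change could be reported as undetected.

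**Working it through.** **Is there a figure in the plan to reproduce?** No. Section 2.7 takes 30 patients from a rule of thumb for single-group pilots (10 to 40). It gives no alpha, power, SD, effect size or correlation.

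**Inputs.** From the article: n = 30 (section 2.7), one group (2.1), two time points for knowledge (2.6.2) and three visits for the scales (2.6.1, 2.6.3, 2.6.4). Assumed here: all 30 patients complete, equal SD at each visit, within-patient correlation r of 0.5 to 0.8, two-sided alpha of 0.05, an illustrative change of 0.5 SD, and the same correlation between every pair of the three visits.

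**Standard error of a mean change, in SD units.**

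- Treated as independent groups: sqrt(2/n) = sqrt(2/30) = 0.258.
- Correct, within patient: sqrt(2(1 − r)/n).
- Ratio: 1/sqrt(1 − r).

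**95% interval.** The independent t has 2 × 30 − 2 = 58 degrees of freedom (critical value 2.002). The paired t has 29 (critical value 2.045). The width ratio is therefore the SE ratio times 2.002/2.045 = 0.979.

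| r | Paired SE | SE ratio | Interval width ratio |
|---|---|---|---|
| 0.5 | 0.183 | 1.41 | 1.38 |
| 0.7 | 0.141 | 1.83 | 1.79 |
| 0.8 | 0.115 | 2.24 | 2.19 |

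Outside the assumed range, the SE ratio is 1.20 at r = 0.3 and 1.00 at r = 0.

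**Two time points, simulated** (bivariate normal, n = 30, 20,000 runs per setting, nominal 5%):

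| r | Type I error, independent t | Type I error, paired t | Power at 0.5 SD, independent t | Power at 0.5 SD, paired t |
|---|---|---|---|---|
| 0.5 | 0.0066 | 0.049 | 0.47 | 0.75 |
| 0.7 | 0.0006 | 0.048 | 0.47 | 0.93 |

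The noncentral t gives the same paired power. The noncentrality is 0.5 × sqrt(30)/sqrt(2(1 − r)), that is 2.74 at r = 0.5 and 3.54 at r = 0.7, for powers of 0.754 and 0.927.

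**Three visits, simulated** (20,000 runs per setting; for power, both later visits are shifted by 0.5 SD):

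| r | Type I error, one-way ANOVA | Type I error, repeated-measures ANOVA | Power, one-way | Power, repeated-measures |
|---|---|---|---|---|
| 0.5 | 0.004 | 0.052 | 0.43 | 0.79 |
| 0.7 | 0.0002 | 0.049 | 0.39 | 0.95 |

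The difference between the two visit means is the same number under either analysis. Only its standard error, interval and p-value change.

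**The case against.** The strongest reply is that section 2.8 is loose rather than wrong. It ties no test to any outcome, Student t is a family name that can include the paired form, and groups may be shorthand for sets of measurements. There are also groups to which the sentence could apply: GOLD 2 and GOLD 3 patients (section 2.3), or patients and researchers, who both rate cost (section 2.8). And this is a condensed article about a feasibility study with no planned power.

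Part of this stands. Because no test is assigned to an outcome, a reader might infer that every standard error and p-value in the study would necessarily be wrong, but the text does not support that. The investigators may intend a paired t, and with zero correlation the two standard errors coincide.

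The reply does not rescue the sentence, however. Its wording describes the independent forms, the article plans no comparison by severity class or by type of rater, and no within-patient test is named for the pre/post aim. Nor is this a detail left to an unseen analysis plan: the article states specific methods, and they do not match its own design.

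Three other inferences are tempting and fail:

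- **False positives.** With positive correlation the mismatch lowers the rejection rate below 5%. It does not raise it.
- **Spoiled planning inputs for the randomised trial.** The outcome SD and the between-visit correlation can be taken from the raw data whichever test is run.
- **Skewed data mishandled.** Section 2.8 limits the t test to normally distributed variables. An article may leave the alternative to the full plan, and the article does not document that any outcome will be skewed.

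**Conclusion.** The point holds as a mismatch between the stated tests and the design. If the tests were applied as worded to the repeated scores, precision and power would be lost: standard errors 1.41 to 2.24 times too large, 95% intervals about 1.38 to 2.19 times too wide, and power for a 0.5 SD change of about 47% instead of 75% (r = 0.5) or 93% (r = 0.7). Type I error would fall to about 0.7% at r = 0.5.

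These sizes rest on the assumed correlation, alpha and effect size, none of which the article gives. The direction needs only a positive within-patient correlation, which is to be expected for the same patient on the same scale. The harm is conservative, leaves the estimated mean change untouched, and can be fully cured before analysis because the data collected are the right data.

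**What to change.** Replace the sentence on tests in section 2.8 with wording such as:

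*Scores taken at two time points are compared by a paired t test, or by the Wilcoxon signed-rank test. CAT, CCQ and HAD at baseline, final consultation and one month are analysed by repeated-measures ANOVA or a linear mixed model with visit as a fixed effect. Any binary item measured twice in the same patients is compared by McNemar's test. Mean within-patient change, its SD and a 95% confidence interval are reported.*

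Either method for the three visits is adequate; the plan should name one. The article identifies no paired binary outcome, so the McNemar clause applies only if there is one. If a comparison of independent groups is really intended, for example by severity class, the section should say so and keep the existing tests for that purpose only.

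This wording is not meant for the counts of hospitalisations and emergency visits, which cover windows of unequal length (the year before, the intervention period and the month after).

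The cost is one paragraph. No new data, staff or software is needed, since SPSS 25 runs all of these methods.
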